#### Data analysis

Data will be entered and then analysed using SPSS Statistics (57). Baseline characteristics and demographic characteristics will be tabulated. Prior to analysis, data will be checked in terms of errors in data entry, missing data, normality and outliers by the lead researcher ([name]). For missing data, intention-to-treat (ITT) analyses will be administered.

#### Data analysis of primary outcomes

The focus will be on tabulated and associated graphical summaries of the key indicators associated with the outcomes of a feasibility trial, which includes participant recruitment and attendance. Specifically, summary statistics will be the total number of referrals to the P-CFT groups, the number of service users who provide consent-to-contact and the number of service-users who provide their informed consent. Furthermore, group attendance and dropout rates, completion of follow-up outcome data and the number of participants who are retained at each timepoint will also be generated.

#### Data analysis of secondary outcomes

Summary statistics of the included measures (FCS-SC, SOCS, PBQ, CORE-10, DASS-21, SWEMWBS, CORE-10) at each timepoint will be presented in tables and/or graphs. Exploratory analyses of these outcomes will be conducted using the appropriate statistical method. The effect sizes generated from the secondary clinical outcomes, particularly the compassion-based measures, will also help to inform power analyses for larger scale definitive trials of P-CFT. To assess the effects of P-CFT at an individual-level, Jacobson and Truax’s (58) reliable change index will be utilised. For each measure, the percentage of participants that report a clinically significant change from Time 1 to Time 2 and Time 3 will be reported.

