### Design

The study will adopt a single pre-post, quasi-experimental study design comprising three components (in this protocol, these components are referred to as Component 1, 2 and 3). This study design provides a convergent-parallel mixed methods process evaluation (30), which encapsulates the assessment of feasibility and acceptability, required as part of the MRC *Framework for Developing and Evaluating Complex Interventions* (29). The convergent-parallel approach entails the collection and analysis of quantitative and qualitative data, which are subsequently integrated and compared to allow for a unified analysis (30). Data from Components 1 and 2 will use quantitative methods and Component 3 will generate qualitative data. **Figure 1** displays an overview of the study design that reflects CONSORT guidelines (31), wherein a schedule of the study enrolment and assessments are provided in **Table 1**.

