### Intervention and its delivery

The intervention is reported in line with the Template for Intervention Description and Replication (TIDieR) checklist (38), (see **Appendix A** in **Supplementary Materials** for further details). The group P-CFT intervention is based on Cree’s (11) adaptation of Gilbert’s (13, 14) CFT (see **Appendix B** for an overview of a P-CFT course). Whilst Cree’s (11) guidance is based on 12 sessions, the number of sessions can vary between services. In this study, the P-CFT intervention will range from eight to 12 sessions, which are to be delivered remotely via online video call platform Microsoft Teams (39) or in-person at a site of the perinatal CMHT. The two-hour sessions are offered once a week in consecutive weeks. There are two group facilitators in each group, and the number of participants can range from four to eight.

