### Component 1: feasibility study

#### Design

This component will use a non-randomised longitudinal, repeated measures design, across three research sites through routinely collected data and self-report outcome measures.

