#### Sample size consideration

Due to this study being a feasibility and acceptability study, formal sample size calculations were not undertaken. During the 28-month recruitment period of this study (from November 2023 to March 2026), it is estimated that approximately 17 groups will be offered across three NHS trusts (with ideally 4–8 participants in each group). Therefore, the potential pool of participants is 64 to 128 participants. It is planned to recruit 50% of this potential pool of participants (*n* = 32), approximately ten to 11 participants per site for baseline recruitment. This sample size reflects the median target baseline recruitment rate of 30 participants for feasibility studies in the United Kingdom (UK) (43). As an important part of the overall study aims to assess the feasibility of recruitment and retention, possible dropouts have not been factored into this calculation.

Retention of participants in the study will be examined using Lewis et al.’s (44) framework for assessing retention as a progression criterion. By applying the ‘traffic light system’, a retention rate above 85% will be considered acceptable (GREEN), 65% to 84% will be considered a borderline level of retention (AMBER), and below 65% (RED) will be deemed as a low level of retention. For any future studies on P-CFT in NHS perinatal services, a GREEN retention rate will indicate that the current study methodology is feasible for participant recruitment. Several amendments may be required to the methodology following an AMBER retention rate. A retention rate of RED demonstrates that considerable changes would be necessary to improve retention of participant recruitment. A preliminary exploration of attrition bias will also be conducted to examine if certain demographics or variables may influence attrition (e.g., number of children, financial situation).

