## Discussion

To the authors’ knowledge, this study will be the first multi-site feasibility and acceptability study of perinatal CFT in specialist perinatal mental health services in NHS England. In general, the study will be able to explore and report if an online delivery of this intervention is beneficial for mothers and birthing parents in a specialist perinatal community mental health team. Specifically, the findings can help identify how the content and/or delivery can be adapted to optimise outcomes for P-CFT attendees. For instance, data collection of attendance levels per session will enable an objective measure of acceptability. An increase in attrition may indicate low acceptability of the content of one of the sessions. Possible observations such as this will be able to be further explored qualitatively. Moreover, service users within these perinatal clinical settings present with a range of mental health difficulties. Through the qualitative data collection, the suitability of P-CFT can be explored trans-diagnostically, allowing for further refinement of service delivery.

The suitability of recruitment methods can also be established to identify the type of recruitment methods that are appropriate for this specific type of intervention and clinical setting. Any potential barriers will be noted. For instance, one question is whether or not the recruitment strategies enable a sufficient sample size to be collected. Exploring potential barriers to recruitment and retention will highlight the type of practical issues that may need to be addressed when conducting any futures studies on P-CFT within a specialist perinatal mental health team for both service-users, staff members, and researchers.

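### Within-group pre-post effect sizes cannot supply the target difference for a definitive trial, and intention-to-treat is not a missing-data method in a study without allocation

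*Protocol article*

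**What the plan says.** The Methods section on design states: "The study will adopt a single pre-post, quasi-experimental study design comprising three components". For Component 1 it adds: "This component will use a non-randomised longitudinal, repeated measures design, across three research sites". There is no comparator. On size, the section Sample size consideration says that "formal sample size calculations were not undertaken" and sets the baseline target: "It is planned to recruit 50% of this potential pool of participants (*n* = 32"). Dropout is not allowed for.

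Under Data analysis of secondary outcomes, the analyses of the clinical measures are called exploratory and no test is named. The same paragraph then gives the results a use: "The effect sizes generated from the secondary clinical outcomes, particularly the compassion-based measures, will also help to inform power analyses for larger scale definitive trials".

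Under Component 1, Data analysis, the one sentence on incomplete data is: "For missing data, intention-to-treat (ITT) analyses will be administered".

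The Discussion says that "the study will be able to explore and report if an online delivery of this intervention is beneficial for mothers and birthing parents". The section Intervention and its delivery allows groups to run by video call "or in-person at a site of the perinatal CMHT".

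**The concern.** Two stated rules do not do what they are meant to do.

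First, a controlled trial is powered on the difference between arms. The effect size from this study will be a change over time in one group. Participants are referred with moderate to severe difficulties, so some regression to the mean is likely. Time since birth passes between assessments. The section Setting says that the same teams also provide other psychological therapy, medication and bonding support. All of this is inside the pre-post change and would also occur, in whole or part, in a control arm. The Introduction itself notes that the two most recent evaluations had no control groups, yet the analysis section gives the same kind of estimate a role in powering the next trial.

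Second, intention-to-treat says which participants are analysed and under which allocation. It does not say what is done when a score is absent, and this study allocates nobody. Missing scores are to be expected: dropout is left out of the sample size, and the Discussion lets participants skip items. As written, the sentence does not choose between approaches that give different answers.

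At stake are the size of the definitive trial and the reading of the change scores. The primary outcomes, which concern feasibility, are not affected by the first point.

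**Working it through.** **The plan's own figure.** 0.50 × 64 = 32, which reproduces the baseline target. There is no power calculation to reproduce. The protocol gives no effect size, SD, correlation between time points or expected retention, so everything below rests on assumed values and is illustrative.

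**1. Precision of a pre-post effect.** For a standardised change d in n people, SE(d) = √(1/n + d²/(2n)). Take d = 0.5 and n = 27, that is 27/32 = 84% retained, close to the boundary between the AMBER and GREEN retention bands. Then SE = √(1/27 + 0.25/54) = √0.04167 = 0.204, and the 95% CI is 0.5 ± 1.96 × 0.204 = 0.10 to 0.90. An exact noncentral-t interval agrees: 0.10 to 0.90 at n = 27, 0.13 to 0.86 at n = 32, and 0.04 to 0.95 at n = 21. Read as a two-arm effect at 80% power, the limits at n = 32 correspond to 952 and 22 per arm. Even before any bias, the estimate says little about the size of a later trial.

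**2. Change that is not due to treatment.** The number per arm for a two-arm comparison, two-sided 5% and 90% power, is 2(1.96 + 1.2816)²/d² = 21.016/d².

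- d = 0.8: 32.8, so 33 per arm
- d = 0.5: 84.06, so 85 per arm
- d = 0.3: 233.5, so 234 per arm

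Suppose 0.8 is observed and used as the target, while 0.3 to 0.5 of it would have happened without P-CFT. Power at 33 per arm is Φ(d√(33/2) − 1.96):

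- true 0.5: Φ(2.031 − 1.96) = 0.53
- true 0.3: Φ(1.219 − 1.96) = 0.23

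A milder set of assumptions points the same way. Take an observed 0.5 and 80% power, so 63 per arm:

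| Change without P-CFT (SD) | Net difference | Needed per arm | Power at 63 per arm |
|---|---|---|---|
| 0 | 0.5 | 63 | 80% |
| 0.1 | 0.4 | 99 | 61% |
| 0.2 | 0.3 | 175 | 39% |
| 0.3 | 0.2 | 393 | 20% |

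**3. Choice of standardiser.** The protocol does not say whether the effect size is divided by the SD of change or the SD of scores. If a change of 0.5 is in units of the SD of change, then on the score scale d = 0.5 × √(2(1 − r)). This gives 0.59, 0.50, 0.39 and 0.32 for r = 0.3, 0.5, 0.7 and 0.8, or 45, 63, 105 and 157 per arm at 80% power. This error can go in either direction.

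**4. What the missing-data sentence leaves open.** Suppose completers change by 0.5. An analysis of completers reports 0.5. Setting dropouts to no change reports 0.5 × 0.85 = 0.425 at 85% retention and 0.5 × 0.65 = 0.325 at 65%. Carried into a two-arm calculation at 80% power, these are 63, 87 and 149 per arm. Naming intention-to-treat does not select among them.

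**5. Online delivery.** Set side by side, the Discussion speaks of benefit from online delivery, the intervention section allows both modes, and the design has no control group and describes no comparison by mode. The data can describe feasibility and acceptability by mode, but not benefit.

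**The case against.** The strongest reply is that the protocol is modest. It says the effect sizes will help to inform power, not that a trial will be sized on them, and it calls the analyses exploratory. That stands. It is also true that SDs, correlations and retention from this sample can properly feed a later calculation, so the data are not useless for that purpose. A reader might infer that a definitive trial is bound to be underpowered. The documents do not support that: they give neither an effect size nor a share of change that is unrelated to treatment, and if that share were zero there would be no loss from this cause.

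On missing data, a reader might infer that incomplete participants will be dropped by paired tests or repeated-measures ANOVA. No such test is named, and imputation or model detail may sit in an analysis plan that is not shown. Sample size consideration also plans a preliminary look at attrition bias. In a single group, intention-to-treat could be read loosely as including everyone enrolled, whatever their attendance. What remains is that this describes an analysis set, while the sentence offers it as the treatment of missing values.

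On online delivery, the sentence is general Discussion text and hedged; the objectives contain no such claim. A reader might infer that delivery mode will go unrecorded because the demographic list omits it. That is not established: mode belongs to the group rather than the participant, and the intervention checklist in Appendix A is not shown.

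**Conclusion.** The point holds in two parts and should be corrected. The within-group change cannot serve as the between-arm target difference, and intention-to-treat is misnamed as a missing-data method. Both follow from the text and need no assumption.

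The size of the consequence does rest on assumptions. Depending on the values taken, power falls from 90% to between 53% and 23%, or from 80% to between 61% and 20%, with no fall if nothing changes without P-CFT. The supported statement is that a trial sized on these effects could be underpowered. The choice of a single-group feasibility design is not at fault; the use made of its effect size is. The online sentence is a minor matter of wording.

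**What to change.** - **Data analysis of secondary outcomes.** State that SDs, Time 1 to Time 2 correlations and retention, each with a confidence interval, will inform the definitive trial; that pre-post effects are descriptive only; and that the target difference will come from a minimum important difference or from controlled evidence.
- **Component 1, Data analysis.** Replace the intention-to-treat sentence with: all consented participants with any score are analysed regardless of attendance, by a likelihood-based mixed model with time fixed and participant random; an analysis of completers is a sensitivity analysis; completion rates use observed data only. Add a therapy-group random effect only if it can be estimated: 32 participants over about 17 groups is roughly two per group (32/17 = 1.9), so it may not be.
- **Discussion.** Limit the statement on online delivery to feasibility and acceptability, described by delivery mode.

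The cost is a few sentences, slightly more analysis work and a more modest claim. Delivery mode is one fact per group and can be noted retrospectively if it has not been kept.

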### Component 2: parent-infant interaction

#### Design

Component 2 will adopt a pre-post recorded observation of parent-infant interactions. Participants will be asked to make two short (six minute) video recordings of interactions between themselves and their infant, one prior to their participation in the CFT group, and one after the group finished.

#### Participant inclusion/exclusion criteria

The inclusion and exclusion criteria applied to the overall study is largely consistent across Component 1 and Component 2. However, participants who are pregnant at baseline (Time 1) are excluded from Component 2, because a recording of the parent-infant dyad is required.

#### Sample size consideration

Of the approximate 32 participants that completing the baseline assessment of Component 1, it is hoped that 50-75% of this sample will also consent to participate in Component 2. Therefore, Component 2 aims to recruit 16–22 parent-infant dyads, with ideally 5–8 participants collected from each research site.

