### Setting

The feasibility and acceptability study will be conducted in NHS specialist perinatal community mental health teams (CMHT) that are offering group P-CFT as an intervention across three NHS trusts located in the northwest, southeast, and southwest of England. In England and Wales, specialist perinatal CMHTs offer multidisciplinary support to mothers, birthing parents, and their families who are experiencing moderate to severe mental health difficulties during pregnancy and at postpartum (8). Furthermore, they can offer treatment to mothers deemed at high-risk of postpartum relapse due to their histories of moderate and severe mental health conditions. This support includes psychological therapies, psychotropic medication, and parent-infant bonding support (8).

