In particular, the feasibility of the online implementation of the MACI, the parent-infant video interactions can be evaluated. In previous studies, the data collection of this tool has primarily been conducted in-person with the participants (60). However, this method was not feasible for this study due to the locations of the recruitment sites. As recruitment is being delivered online, some novel aspects require evaluation for feasibility. Srikar et al. (59) reported that an online/remote version of the MACI-Infant measure was feasible to use in mothers with infants at elevated likelihood of autism. Nevertheless, it is unclear if an online/remote delivery of the MACI-Infant is feasible among mothers with perinatal mental health difficulties. From a practical perspective, this current study will look at aspects such as whether or not the interaction can be sufficiently set up remotely by participants, whether the self-recordings can be correctly recorded and sent to the researchers through their home devices and the suitability of recording through teleconferencing software, and generally, whether this method is acceptable among the group of mothers and birthing parents. As Component 2 is an optional aspect of the study, the recruitment rate will be able to indicate the willingness of participants to take part in a caregiver-infant interaction study. A meta-synthesis of parental experiences of video feedback parenting interventions highlighted that participating in recorded video interactions can often elicit feelings of self-doubt and anxiety (71). The implementation of remote data collection may help to mitigate this potential issue.

It is important to identify the appropriate outcome measures for perinatal mothers and birthing parents experiencing mental health difficulties. Some of the outcome measures and/or their specific items may elicit distress in participants. By allowing the participants to skip items that they may not be comfortable in answering, the study can determine which specific items or questionnaires are acceptable in this population.

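### The Component 2 dyad target is set on all 32 or so Component 1 participants, including pregnant participants who cannot join, and its upper end is not 75% of 32

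*Protocol article*

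**What the plan says.** The sample size section for Component 2 takes as its base everyone expected to finish the Component 1 baseline measures, about 32 people. On the expected uptake it says: "it is hoped that 50-75% of this sample will also consent to participate in Component 2". It then draws the target as a consequence: "Component 2 aims to recruit 16–22 parent-infant dyads, with ideally 5–8 participants collected from each research site". The Setting section gives the number of sites: "across three NHS trusts located in the northwest, southeast, and southwest of England".

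The eligibility criteria for Component 1 admit two groups: mothers with a baby under two years old, and those currently pregnant who can finish the intervention by about 34 weeks' gestation. The eligibility section for Component 2 then removes the second group: "participants who are pregnant at baseline (Time 1) are excluded from Component 2". The sample size section that follows directly makes no allowance for this.

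The first objective, at the end of the Introduction, names recruitment rates as a feasibility measure for Components 1 and 2. The Discussion says how the Component 2 rate will be read: "the recruitment rate will be able to indicate the willingness of participants to take part in a caregiver-infant interaction study". It states no denominator for that rate.

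**The concern.** A consent percentage is informative about willingness only among people who could have consented. Pregnant participants have no infant to film at baseline and are excluded by rule. The only base that the article gives for Component 2 uptake nevertheless includes them. If the reported rate uses that base, it mixes two different quantities: how many Component 1 participants can take part, and how many of those agree to. A team planning a larger study could then conclude that mothers are more reluctant to be filmed than they are.

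Separately, the target is presented as following from the percentages, and at its upper end it does not. A reader who later compares recruitment with the plan has two upper limits to choose from.

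**Working it through.** **Inputs.** From the Component 2 sample size section: base about 32; hoped uptake 50–75%; target 16–22 dyads; 5–8 per site. From Setting: three sites. The share of the 32 who are pregnant at baseline, *p*, is not in the document. It is an assumption here, shown from 0% to 30%.

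**Step 1: reproduce the stated target.**
- Lower end: 0.50 × 32 = 16, as stated.
- Upper end: 0.75 × 32 = 24, against the stated 22. Conversely, 22/32 = 68.75%.
- No single base gives both ends: 16/0.50 = 32, but 22/0.75 = 29.3.
- By site: 3 × 5 = 15 and 3 × 8 = 24. The upper end agrees with 24; the lower end is one below 16.

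**Step 2: restrict the base to those not pregnant.** The eligible number is E = 32 × (1 − *p*). The target becomes 0.50 × E to 0.75 × E. The uptake needed among eligible participants to reach the stated 16–22 is 16/E to 22/E.

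**Step 3: effect on the rate if it is divided by all 32.** Apparent uptake = true uptake × (1 − *p*).

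| Assumed *p* | E | 50–75% of E | Uptake needed for 16–22 | True 50% / 75% appears as |
|---|---|---|---|---|
| 0% | 32.0 | 16.0–24.0 | 50–69% | 50% / 75% |
| 5% | 30.4 | 15.2–22.8 | 53–72% | 47.5% / 71% |
| 10% | 28.8 | 14.4–21.6 | 56–76% | 45% / 67.5% |
| 20% | 25.6 | 12.8–19.2 | 63–86% | 40% / 60% |
| 30% | 22.4 | 11.2–16.8 | 71–98% | 35% / 52.5% |

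As a check of one row, at *p* = 20%: E = 32 × 0.80 = 25.6; 0.50 × 25.6 = 12.8; 16/25.6 = 62.5%; 0.50 × 0.80 = 40%.

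**Step 4: a possible further restriction.** The Component 2 outcomes section describes the video coding scheme as suitable for infants of 3 to 15 months, while Component 1 admits infants up to two years and the Component 2 criteria state no narrower age limit. If an age limit is applied, *p* in the formulas becomes the total ineligible share, and the base shrinks further.

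**The case against.** The strongest reply is that the sample size section is a forecast, worded as a hope and an aim on an approximate base. An overall yield from 32 recruits is a legitimate planning quantity, and a range of 50–75% leaves room for non-participation for any reason, pregnancy included. The Discussion fixes no denominator, so the investigators could divide by eligible participants without contradicting any sentence. The exact denominator of a descriptive rate is also something an article may leave to the full protocol.

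Much of this stands. A reader might infer that reported willingness will necessarily be understated and then judged against a wrong benchmark. The document does not support that. The understatement arises only if the rate is taken on the base used for the target. The sole progression criterion in the article, the traffic-light rule, concerns retention; nothing passes or fails on Component 2 uptake.

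It is also fair that the slip at the upper end is two dyads, that no power or precision rests on it, and that 5–8 per site could be read as whole numbers enclosing 16/3 = 5.3 and 22/3 = 7.3. The pregnant share may be modest: with eight to 12 weekly sessions to be finished by about 34 weeks, pregnant participants would have to start by roughly 22 to 26 weeks (34 − 12 and 34 − 8).

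What the reply does not remove is that the article uses a base that its own eligibility rule contradicts, and gives a target that does not follow from its own percentages. Nor does anything in the text suggest that 22 was lowered from 24 to allow for pregnancy; the target is derived from 32.

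**Conclusion.** The point holds as an inconsistency in the stated target and a risk to how one feasibility rate is interpreted. The upper end should be 24 if all 32 are eligible, and lower than that otherwise; the stated 22 corresponds to about 69% of 32. On an eligible-only base, 50–75% is about 14–22 dyads if 10% are pregnant and about 13–19 if 20% are. If the Component 2 rate is divided by all Component 1 participants, a true uptake of 50–75% is understated by 5 to 7.5 percentage points at 10% pregnant and by 10 to 15 points at 20%.

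The two arithmetic facts, 75% of 32 and the conflict between base and exclusion, need no assumption. The size of the understatement rests on two: the pregnant share, which the document does not give, and the use of the sample size section's base as denominator, which the Discussion neither states nor rules out. Of the two, the denominator is the main issue and the two-dyad slip is minor.

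**What to change.** 1. Define Component 2 uptake as the number consenting to Component 2 divided by the Component 1 participants eligible for it: those not pregnant at Time 1 and, once the Component 1 age criterion and the stated age range of the video measure have been reconciled, those meeting any infant-age limit that results.
2. Report the number ineligible for Component 2 separately, with the reason.
3. Restate the dyad target as 50–75% of the expected eligible number. This is 16–24 only if all 32 are eligible and proportionately lower otherwise. Bring the per-site figure into line with it.

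This needs a change of wording and of denominator, and should need no new data collection: pregnancy bears on study eligibility, and the age of the youngest child is already asked in the socio-demographic questionnaire. The downside is a smaller stated dyad target, about 11–17 at the 30% end of the assumed range.
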